## Abstract

**Background:**

Until recently, Zika virus (ZIKV) infections were considered mild and self-limiting. Since 2015, they have been associated with an increase in microcephaly and other birth defects in newborns. While this association has been observed in case reports and epidemiological studies, the nature and extent of the relationship between ZIKV and adverse pregnancy and pediatric health outcomes is not well understood. With the unique opportunity to prospectively explore the full spectrum of issues related to ZIKV exposure during pregnancy, we undertook a multi-country, prospective cohort study to evaluate the association between ZIKV and pregnancy, neonatal, and infant outcomes.

**Methods:**

At research sites in ZIKV endemic regions of Brazil (4 sites), Colombia, Guatemala, Nicaragua, Puerto Rico (2 sites), and Peru, up to 10,000 pregnant women will be recruited and consented in the first and early second trimesters of pregnancy and then followed through delivery up to 6 weeks post-partum; their infants will be followed until at least 1 year of age. Pregnant women with symptomatic ZIKV infection confirmed by presence of ZIKV RNA and/or IgM for ZIKV will also be enrolled, regardless of gestational age. Participants will be tested monthly for ZIKV infection; additional demographic, physical, laboratory and environmental data will be collected to assess the potential interaction of these variables with ZIKV infection. Delivery outcomes and detailed infant assessments, including physical and neurological outcomes, will be obtained.

**Discussion:**

With the emergence of ZIKV in the Americas and its association with adverse pregnancy outcomes in this region, a much better understanding of the spectrum of clinical outcomes associated with exposure to ZIKV during pregnancy is needed. This cohort study will provide information about maternal, fetal, and infant outcomes related to ZIKV infection, including congenital ZIKV syndrome, and manifestations that are not detectable at birth but may appear during the first year of life. In addition, the flexibility of the study design has provided an opportunity to modify study parameters in real time to provide rigorous research data to answer the most critical questions about the impact of congenital ZIKV exposure.

**Trial registration:**

NCT02856984. Registered August 5, 2016. Retrospectively registered.

## Background

Until recently, Zika virus (ZIKV) infections were considered mild and self-limiting; however, since 2015, they have been associated with an increase in microcephaly and other birth defects in newborns [1–6].

ZIKV, first identified in 1947 in Uganda, is a single-stranded RNA virus of the RNA virus family *Flaviviridae* that includes other human pathogenic viruses such as dengue virus (DENV) and West Nile virus (WNV) [7]. Between the first isolation of ZIKV in monkeys in 1947 until 2007, reports of human cases had been sporadic [1, 2]. Although the virus was isolated widely in Africa and Southeast Asia, infections were largely asymptomatic, and no epidemics had been observed [1, 2]. Then, in 2007, an outbreak of the Asian lineage of ZIKV occurred in Federated States of Micronesia. In French Polynesia, more than 30,000 suspected ZIKV cases were reported within a 6-month period in 2013 [8].

There were no reported cases of ZIKV in the Western Hemisphere prior to 2014. The first cases of ZIKV in the Americas were reported in northeast Brazil in 2015 [9–11]. Because of the lack of immunity in the population, and the abundance of *Aedes aegypti* mosquitos in Brazil, an autochthonous transmission was established with ensuing widespread dissemination of ZIKV [9]. Although initially concentrated in northeastern Brazil, the virus has since spread throughout South and Central America, the Caribbean, and Puerto Rico [10].

With the introduction of ZIKV, Brazil witnessed an epidemic of microcephaly cases among newborns. In 2015, the Brazilian Ministry of Health (MoH) observed an increased incidence of microcephaly in newborns in the northeastern part of the country in the states of Pernambuco, Paraíba and Rio Grande do Norte, in association with clusters of ZIKV-like illness in pregnant women [12]. To evaluate the association between microcephaly and congenital Zika virus infection, investigators in Pernambuco carried out a case-control study among 91 microcephaly cases (defined as head circumference of 2 or more standard deviations below the mean, per Intergrowth-21 standards) and 173 controls. The results of this study showed a strong association between microcephaly and laboratory confirmed Zika virus infection (Odds Ratio: 73.1; 95% CI 13·0–∞), after adjusting for confounders, and none of the other risk factors studied, including use of the larvicide, pyriproxyfen, nor vaccine administration during pregnancy, was associated with microcephaly in multivariable analyses [13].

Microcephaly had not been associated with ZIKV infection prior to the outbreak in the Americas, but this association had not been examined systematically during previous outbreaks. Using evidence available as of early 2016, Rasmussen et al. used Shepherd’s criteria and Bradford Hill criteria to infer a causal relationship between prenatal ZIKV infection and birth defects [14]. In a recent retrospective review, Besnard et al. described 10 cases of congenital cerebral malformations in fetuses and newborns from the 2013–2014 ZIKV outbreak in French Polynesia [15]. Congenital abnormalities associated with ZIKV infection have since been reported in Colombia and the United States, and in other countries in South America [11, 12, 16–18]. Of 972 pregnant women enrolled in the US Zika Pregnancy Registry (USZPR) with laboratory evidence of a possible ZIKV infection, 5% had a fetus or infant with evidence of a ZIKV-related birth defect [19]. A higher than expected prevalence of microcephaly was observed in Cali and Bogota, Colombia, during the peak ZIKV epidemic period [1].

“Congenital Zika syndrome” (CZS) reflects a pattern of birth defects observed in affected infants [20, 21]. The full spectrum of fetal and infant outcomes associated with ZIKV infection during pregnancy is currently unknown, but recent studies have observed a range of outcomes, including brain abnormalities and neural tube defects, ocular abnormalities, and symptoms related to central nervous system dysfunction (e.g. arthrogryposis, deafness, and microcephaly resulting from fetal brain disruption sequence) [22, 23]. In a study of 46 presumed CZS cases age 1 to 8 months in Maranhão, Brazil, the most commonly observed central nervous system symptoms were irritability (85%), pyramidal/extrapyramidal syndrome (56%), epileptic seizures (50%) and dysphagia (15%) [2].

Infants with ZIKV-associated microcephaly may have comorbid ocular and hearing abnormalities. In a study conducted in Salvador, Brazil, 10 out of 29 infants with presumed ZIKV-associated microcephaly had ocular abnormalities [24]. In a study of the infants of 112 ZIKV-infected mothers, 24 had eye abnormalities, and the presence of abnormalities was associated with microcephaly (odds ratio: 19.1; 95% CI, 6.0–61.0) [25]. Among 69 infants aged 0–10 months with microcephaly and laboratory evidence of ZIKV infection, 4 had sensorineural hearing loss [26]. In imaging studies, brain abnormalities such as intracranial calcifications, cerebral atrophy, corpus collosum abnormalities, cortical malformations, ventriculomegaly, and hydrocephaly, have been observed among fetuses and neonates with presumed in utero exposure to ZIKV [16, 27–29].

To date, most studies have included only symptomatic women. A report of 88 pregnant women with a rash in Rio de Janeiro revealed that 82% tested positive for ZIKV in blood or urine. In addition to rash, women had arthralgias, conjunctival injection, and headache [30]. Twenty-nine percent of ZIKV-positive women had abnormal ultrasounds with corresponding adverse outcome of pregnancies (fetal demise or newborns with confirmed pathology). A cohort study of pregnant women with rash in Rio de Janeiro, Brazil, reported the findings of 134 ZIKV-positive women and 73 ZIKV-negative women [11]. Among 125 ZIKV-positive women for whom outcomes of pregnancy were available, adverse pregnancy outcomes were observed in 46.4%, and among 117 live-born infants, 42% had abnormalities on clinical examination, imaging, or both; 3.4% had microcephaly. Thus, self-limited symptomatic infections during pregnancy were associated with severe outcomes in the fetus. Information is limited about the incidence of fetal abnormalities among women who have asymptomatic ZIKV infection during their pregnancy. In the USZPR study, birth defects were reported in similar proportions of fetuses/infants whose mothers did and did not report symptoms [19]. Other studies have not been able to capture data on asymptomatic women.

Increasing evidence points to ZIKV as the agent responsible for a variety of birth defects in newborns of mothers who become infected during pregnancy [16, 31, 32]. However, the strength of the causal relationship of ZIKV infections in pregnancy with adverse outcomes has yet to be determined. Most studies to date have followed women known to be infected or infants who were born with serious birth defects. Previous studies have not been able to determine differences in risk of ZIKV-associated outcomes by trimester of infection, the rate of vertical transmission and factors that affect this rate, and the full spectrum of infant health outcomes associated with congenital ZIKV exposure.

To address these gaps, we have undertaken a prospective cohort study among pregnant women in areas in Latin America with local ZIKV transmission, including Brazil, Colombia, Guatemala, Nicaragua, Puerto Rico, and Peru. The overall objective of this multisite, multi-country Zika in Infants and Pregnancy (ZIP) study is to assess the strength of the association of ZIKV infection during pregnancy with adverse maternal, fetal, and infant outcomes and the risk of vertical transmission overall, by gestational age, and by presence of symptoms during pregnancy.

## Methods

### Study design

This prospective, international, multisite cohort Zika in Infants and Pregnancy (ZIP) study will recruit up to 10,000 pregnant women from ZIKV-endemic regions and follow them longitudinally throughout pregnancy, delivery, and 6 weeks postpartum. Putative cases of ZIKV infection among pregnant women will be identified by monitoring for symptoms of ZIKV-like illness and performing serial laboratory sampling for diagnosis of seroconversion and viral shedding. Infants born to women enrolled in the study will be followed through 1 year of age and evaluated for neurological, audiological, ophthalmological, and other clinical outcomes.

### Study population

ZIP will recruit pregnant women within the first or early second trimester (up to and including 17 weeks and 6 days), age 15 years and older (with assent and consent as required per local country regulations). Additionally, any pregnant women, regardless of gestational age, with acute Zika-like symptoms confirmed by serology and/or RT-PCR are eligible. Recruitment will occur at hospitals and health clinics across Brazil, Colombia, Guatemala, Nicaragua, Puerto Rico, and Peru. At each of these sites, participants may be referred to this study from surrounding clinical centers. Any pregnant women enrolled in other clinical research (including other Zika studies) requiring blood sampling that, in combination with ZIP requirements, exceeds 50 cc every 8 weeks will not be included in ZIP. Women who indicate at screening that they cannot adhere to the proposed visit schedule are also excluded from the study. Infants are eligible for enrollment if they were born to women enrolled in ZIP and have parental consent.

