### Statistical considerations

#### Study outcome measures

The primary composite endpoint is defined as the occurrence of congenital malformations and adverse fetal and neonatal outcomes. This includes microcephaly, fetal demise, neonatal death (within first 28 days of life), CNS malformations, hydrops, ocular and hearing abnormalities, infant seizures and arthrogryposis.

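### The late, symptomatic entry route admits only infected women and sets no condition on fetal status, so anomalies seen before entry count as events on the exposed side alone

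*Protocol article*

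**What the plan says.** Study population gives two entry routes. The ordinary one runs up to 17 weeks and 6 days. The second is open throughout pregnancy: "any pregnant women, regardless of gestational age, with acute Zika-like symptoms confirmed by serology and/or RT-PCR are eligible". Referral is allowed at every site: "At each of these sites, participants may be referred to this study from surrounding clinical centers".

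Two exclusions are stated. One concerns other research "requiring blood sampling that, in combination with ZIP requirements, exceeds 50 cc every 8 weeks will not be included in ZIP". The other is: "Women who indicate at screening that they cannot adhere to the proposed visit schedule are also excluded from the study".

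Study outcome measures defines the endpoint by occurrence: "The primary composite endpoint is defined as the occurrence of congenital malformations and adverse fetal and neonatal outcomes". It lists the components as follows: "This includes microcephaly, fetal demise, neonatal death (within first 28 days of life), CNS malformations, hydrops, ocular and hearing abnormalities, infant seizures and arthrogryposis". It does not say when a component must first appear relative to enrolment.

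Analyses adjusts for site, maternal age, season or month of enrolment, CMV and DENV, and promises to handle loss to follow-up, fetal loss before 20 weeks and propensity for exposure. It names no term for entry route, reason for referral or fetal status at entry. Study procedures asks for at least one ultrasound per trimester but does not tie it to eligibility or to a baseline assessment.

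**The concern.** The study is a prospective cohort, and the text introducing Table 4 describes the symptomatic comparison as one of incidence. That requires outcomes to be unknown when a woman enters. The late route does not secure this. Several components can be visible on a scan well before a woman at, say, 26 weeks is referred, and nothing stops a known finding from influencing the referral.

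The problem is one-sided. An uninfected woman cannot enter after 17 weeks and 6 days, so any pre-entry anomaly brought in by this route falls in the infected group, and also in the symptomatic group. Selection on an outcome already present cannot be repaired by modelling who becomes infected, which is what a propensity for exposure does.

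The Background criticises earlier work for starting from women known to be infected or infants already affected; this route partly brings that selection back. Sample size considerations allows recruitment to be focused on symptomatic women if rates differ from projection, which would enlarge the route.

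**Working it through.** **Inputs.** From Sample size calculations for primary objectives: Fisher's exact test, two-sided 0.05, background risk 1%. Infection contrast (Table 3): 25% infected of 8,000, that is 2,000 against 6,000. Symptomatic contrast (Table 4): 3% of 10,000, that is 300 against 9,700. The number k of late-route women with an anomaly known before entry is not in the documents and is assumed.

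**Plan's own figures first.** Exact enumeration of Fisher's test over two binomials gives:
- 2,000 against 6,000, 2% against 1%: power 89.7% (stated 90%).
- 300 against 9,700, 3% against 1%: power 77.5% (stated 77%).

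**Effect of k under a true null.** Let both groups have 1% risk and add k already affected women to the exposed group of size n. The expected exposed risk is (0.01n + k)/(n + k), and the apparent risk ratio is that divided by 0.01. The rejection probability comes from the same enumeration.

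| Contrast | k | Exposed risk | Apparent RR | Rejection |
|---|---|---|---|---|
| 2,000 v 6,000 | 0 | 20/2,000 = 1.00% | 1.00 | 4.3% |
| | 2 | 22/2,002 = 1.10% | 1.10 | 5.5% |
| | 5 | 25/2,005 = 1.25% | 1.25 | 13.0% |
| | 10 | 30/2,010 = 1.49% | 1.49 | 40.7% |
| 300 v 9,700 | 0 | 3/300 = 1.00% | 1.00 | 3.1% |
| | 2 | 5/302 = 1.66% | 1.66 | 16.9% |
| | 3 | 6/303 = 1.98% | 1.98 | 31.9% |

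The same women enter both contrasts. Two of them barely move the infection contrast but raise false rejection in the symptomatic contrast more than fivefold (16.9/3.1 = 5.5).

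**Early route, for comparison.** A malformation present before any infection should be about equally frequent in women later infected and women never infected. Adding a common rate q to true risks of 2% and 1% gives RR = (0.02 + q)/(0.01 + q). With q = 0.5% (assumed), RR = 0.025/0.015 = 1.67 and power at 8,000 is 79.6%. With q = 1%, RR = 0.03/0.02 = 1.50 and power is 70.3%. The direction is dilution, not inflation.

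**The case against.** **Late entry is narrower than it may seem.** A reader might infer that a positive test plus an abnormal scan is enough for late entry. It is not: the woman must have acute symptoms confirmed by the laboratory, and those symptoms are an ordinary reason for referral in themselves. This stands and narrows the pathway. It does not close it, because no fetal criterion accompanies the symptom requirement.

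**Large k is hard to reach.** If anomalies are unrelated to Zika and composite risk is 1%, supplying 10 affected women takes at least 10/0.01 = 1,000 symptomatic infected pregnancies, with every event visible before birth and every one referred. Twenty takes 2,000. Table 4 assumes 3% to 5% symptomatic, or 300 to 500 of 10,000. Neonatal death, seizures and hearing loss cannot be seen before birth, so the true requirement is higher. This weighs against the top of the range. It is not a firm bound, because referrals come from surrounding centres whose size is not given and Table 4's share describes the enrolled cohort.

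**Both routes inflate the association.** A reader might infer this too. The documents do not support it: early-route malformations that precede infection fall on both groups and mainly dilute the ratio.

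**The article is condensed.** The full protocol may hold an onset rule, and the article promises further pre-specified covariates and sensitivity analyses. All clinical ultrasounds are recorded, so much of the needed data may already be collected. That is fair. But the article does state its eligibility criteria, endpoint and main covariates, and as stated they leave the late route open.

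**Referral may not depend on fetal findings.** No passage says that it does. The bias away from the null is conditional on this.

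**Conclusion.** The point holds for the late route. A one-sided entry path, no fetal-status condition, an endpoint without an onset rule and no relevant adjustment together allow outcomes known before enrolment to count as events in the exposed groups only. If referral depends even partly on a fetal finding, both primary associations are biased away from the null.

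The size is a sensitivity range, not an estimate, and rests on the plan's 1% background risk, its group sizes and an assumed k. Five to 10 such women would produce an apparent risk ratio of about 1.25 to 1.5 for infection, and 2 or 3 about 1.7 to 2.0 for symptomatic infection. The symptomatic contrast is the more fragile. The documents do not show that such referrals occurred, or that the early route inflates the association.

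**What to change.** - **At entry**, record the entry route, the reason for referral, and the date and result of the last ultrasound.
- **Primary contrasts:** women entering by the late route with a composite component documented at or before entry stay enrolled for descriptive and infant follow-up but are left out of the two primary contrasts.
- **Sensitivity analyses:** (a) early-route entrants only; (b) anomalies documented at or before the entry visit removed in both exposure groups alike; (c) the excluded late-route women put back, to show the difference.

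Two tempting alternatives should be avoided. Counting a malformation only if it was not documented before the infection date works on infected women alone, since uninfected women have no such date, and would bias the ratio downwards. Excluding every pre-entry finding on both routes from the primary analysis could remove true effects of early infection, so that belongs in sensitivity analysis (b).

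The cost is one analysis-set rule and a few entry-form items, largely taken from existing scans. A few late-route women are lost from the primary analysis, some of whose anomalies may be true effects of infection. Those who remain are selected as free of a documented anomaly at entry, which may pull the estimate towards the null. Analyses (a) and (c) show how much these choices matter.

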### Study objectives

#### Primary objectives

To compare the occurrence of congenital malformations and adverse outcomes (including microcephaly, fetal demise, neonatal death, CNS malformations, hydrops, and ocular abnormalities) in fetuses/infants of women who become infected with ZIKV during pregnancy compared to women who do not.To compare the occurrence of congenital malformations and adverse outcomes in fetuses/infants of women who become symptomatic with ZIKV infection during pregnancy versus those who do not.

#### Secondary objectives

To determine the long-term clinical sequelae among infected infants.To determine the rate of ZIKV seroconversion among pregnant women from ZIKV-endemic regions.To compare the severity of maternal and infant outcomes by gestational age, stratified by symptomatic and asymptomatic ZIKV infection.To compare occurrence of adverse maternal and fetal outcomes (including preeclampsia, preterm birth, intrauterine growth restriction (IUGR), and oligohydramnios/polyhydramnios) between women who become infected with ZIKV infection during pregnancy and women who do not.To compare occurrence of adverse maternal and fetal outcomes (including preeclampsia, preterm birth, IUGR, and oligohydramnios/polyhydramnios) between women with symptomatic vs. asymptomatic ZIKV infection.To determine if coinfections and cofactors (including social and environmental factors) contribute to the presence and severity of CNS malformations and disease in the offspring.To determine the duration of ZIKV persistence and shedding during pregnancy in blood, urine, genital secretions, and saliva.To determine whether mothers with ZIKV infection prior to or after delivery shed virus in breast milk and to determine the incidence of postpartum infant ZIKV infection acquisition.

### Study procedures

At study entry, women will be interviewed or have data abstracted about their medical, vaccination, and pregnancy history. At each monthly visit during pregnancy, at delivery, and 6-weeks (+/− 2 weeks) post-partum, women will have a physical exam or have data abstracted from their medical chart and be administered a health questionnaire on general and pregnancy health indicators, exposure to environmental hazards, and evidence of prior ZIKV symptoms. All women will have samples (blood, urine, saliva, and vaginal fluids) collected for assessment of ZIKV and other potential infections (i.e., Toxoplasmosis, Rubella, Cytomegalovirus (CMV), and Herpes Simplex Virus (HSV) (TORCH) and syphilis), and environmental exposures. Additional TORCH testing may be conducted per the local standard of care. Detailed delivery information will be obtained about delivery circumstances and outcomes.

If women note that they will be getting an amniocentesis for clinical care, the study team will coordinate with the participant and her obstetrician to obtain a sample of fluid for testing for ZIKV infection. Breastmilk will be collected, if possible, at the delivery and 6-weeks post-partum visit. If the delivery is a live birth, cord blood, placental tissue, and amniotic fluid will be collected during the delivery visit, if possible. Fetal tissues will be collected, if possible, in the event of a fetal loss.

In between monthly visits, women will provide a urine sample, which is collected at home and brought to the next monthly visit or collected at a biweekly visit in the clinic. This sample will be retrospectively tested for ZIKV if she has a serologically positive test for ZIKV at a monthly visit. Women will also be asked to keep track of potential ZIKV symptoms using a symptom journal in between visits.

Pregnancies will be followed by ultrasound at study visits in accordance with local clinical standard of care. All clinical ultrasounds will be recorded; at a minimum one ultrasound per trimester will be obtained. Women will be educated about Zika prevention, signs and symptoms and queried for signs and symptoms of ZIKV infection and pregnancy complications at each visit. Women experiencing Zika-like symptoms in between study visits will be instructed to come to the clinic immediately to provide specimens for testing.

Women testing positive for ZIKV will be scheduled for two additional clinic visits within 2 weeks for collection of additional blood, urine, saliva, vaginal fluid samples and a fetal ultrasound, per country and local guidelines. In addition, the MoH and local health jurisdictions will be informed per in-country regulations/requirements. Following local regulatory requirements, participants will be given their test results and counseled as needed to explain test results. Counseling may include information about the limitations in interpretation of the assays and provision of social support, as appropriate.

Infants will be assessed for ZIKV infection at birth with laboratory assessment from cord blood or peripheral blood, urine, and saliva. They will be evaluated for signs and symptoms of neurological abnormalities and will undergo auditory and visual screening. In addition, infants will be seen at 3, 6, and 12 months for a general physical exam; neurological assessment; auditory, visual, and neurodevelopmental screening assessments; and laboratory testing. If auditory, visual, or neurodevelopmental evaluations are abnormal, infants will be referred for additional testing and results recorded. Data from any radiological testing for infants with ZIKV exposure done for clinical care will be recorded. Infants noted to have any deficits will undergo appropriate follow-up and testing. If cerebrospinal fluid (CSF) is collected per clinical guidelines, remaining CSF will be stored in the study bio-repository for future testing.

See Tables 1 and 2 for additional information about data and specimen collection.

**Table 1 Tab1:** Data collection details

Assessment	Time frame	Data collected
Maternal Data		
Demographic Survey	Study entry	Basic demographics, e.g., age, race and ethnicity, marital status, and education
Medical History	Study entry	History of: significant medical disorders; previous DENV or Yellow Fever infections and vaccination; any prior infections with parvovirus, herpes, cytomegalovirus, and syphilis
Physical examination and Zika-like symptoms questionnaire	All visits	Assessment of general appearance, including height and weight, and blood pressure and temperature; history of recent symptoms consistent with ZIKV infections, including rash, fever, arthralgias, eye pain, and conjunctivitis
Pregnancy questionnaire	Monthly visits	Signs/ symptoms of pregnancy complications, including decrease in fetal movement, rupture of membranes, vaginal bleeding, headaches, scotomata, nausea, and vomiting.
Imaging assessments	Once per trimester	Ultrasound results
Environmental/ occupational exposure survey	Once per trimester	Participant’s and her domestic partner’s occupational history; household characteristics; behavioral risk factors (e.g. drinking, smoking); exposure to animals in the home; and exposure to known environmental chemicals
Delivery (live birth or fetal loss) information	At delivery	Mode, location, and outcome of the delivery
Infant Data		
Physical examination and growth parameters	All visits	Examination of cardiac, respiratory, and other systems, and skin and gastrointestinal conditions; weight, length or height, and head circumference; gestational age at birth and Apgar scores (birth visit only)
Hearing, ophthalmologic, and neurological assessments	All visits	General motor development markers, including lethargy, seizures, reflexes, etc.; hearing assessments (otoacoustic emission or automated auditory brainstem response); general eye exams; and ophthalmologic exams to detect chorioretinitis or abnormalities in conjunctiva, lens, or retina. If initial exams are abnormal, infants will be referred for additional audiology and/or ophthalmology testing, and results (if available) from any tests done for clinical reasons will be recorded.
Imaging studies	As done per local standard of care	Any imaging assessments done for clinical care, including any neuroimaging studies (ultrasound, CT, or MRI) obtained for clinical reasons to detect neurologic abnormalities such as intracranial calcifications.
Neurodevelopmental assessment	3, 6, and 12- month visits	Screening neurodevelopmental assessments (Ages and Stages Questionnaire or the Bayley Infant Neurodevelopmental Screener) of all study participants. If results of screening assessment are abnormal, the infant will be referred for diagnostic neurodevelopmental testing using the Bayley Scales of Infant and Toddler Development (BSID) -III.

**Table 2 Tab2:** Specimen collection schedules

Maternal specimen collection schedule							
		First trimester < 14 weeks	Second Trimester < 28 weeks gestation	Third Trimester 28 weeks and greater	Delivery: live birth or fetal loss	6 weeks postpartum +/− 14 days	Zika symptomatic visits
	Screening & Entry	Monthly visits	Monthly visits	Monthly visits			
Serum, plasma, whole blood, urine, saliva, vaginal swab	X	X	X	X	X	X	X
Breast milk					X	X	
Amniotic fluid (if possible)			Only if amniocentesis was performed for clinical care		X		
Cord blood (if possible)					X		
Placenta and fetal tissue if fetal loss (if possible)					X		
Infant specimen collection schedule							
	Birth	3 months		6 months			12 months
Urine, saliva, serum	X	X		X			X
Cerebrospinal fluid (remnant specimen)	Only if collected for clinical care	Only if collected for clinical care		Only if collected for clinical care			Only if collected for clinical care

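### Detection of the imaging-found parts of the primary composite can depend on ZIKV exposure, and the text and Table 1 conflict on whose infant imaging is recorded

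*Protocol article*

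**What the plan says.** **Fetal imaging.** Study procedures sets a floor for every woman and records scans whatever the exposure: "All clinical ultrasounds will be recorded; at a minimum one ultrasound per trimester will be obtained". It then adds visits that depend on the test result: "Women testing positive for ZIKV will be scheduled for two additional clinic visits within 2 weeks". Those visits include "vaginal fluid samples and a fetal ultrasound, per country and local guidelines".

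**Infant imaging, text.** The same section says: "Data from any radiological testing for infants with ZIKV exposure done for clinical care will be recorded".

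**Infant imaging, Table 1.** The imaging row under Infant Data covers "Any imaging assessments done for clinical care, including any neuroimaging studies (ultrasound, CT, or MRI) obtained for clinical reasons". Its time frame is "As done per local standard of care". Neither entry mentions exposure.

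**Other infant assessments.** Growth, head circumference, neurological, hearing and eye assessments are listed for all infant visits (birth, 3, 6 and 12 months) without reference to exposure.

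**Endpoint and analysis.** Study outcome measures lists microcephaly, fetal demise, neonatal death, CNS malformations, hydrops, ocular and hearing abnormalities, seizures and arthrogryposis. Analyses names adjustment for site, maternal age, season or month of enrollment, and CMV and DENV infection, and says that loss to follow-up, early fetal loss and propensity for exposure will be handled. Sensitivity analyses are promised in general terms.

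**The concern.** The primary comparison is between infected and uninfected women, so the outcome should be looked for equally hard in both. Three features work against that for CNS malformations and hydrops:

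- A fetal scan is triggered by the exposure itself.
- No infant imaging is scheduled for everyone. It is done when local care calls for it, and women are told their ZIKV results, so known exposure can prompt imaging.
- The text and Table 1 disagree on which infants have their clinical imaging recorded. A site following the text has no instruction to enter a lesion seen in an unexposed infant. A site following Table 1 would enter it.

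The first two affect whether a lesion is found, and the third whether a found lesion reaches the database. All three push in the same direction, toward more events in the infected group. The planned effect is small in absolute terms (1% against 2%), so a few extra detected events matter. Adjusting for maternal covariates or for propensity to be exposed does not correct unequal detection, and imaging that was never recorded cannot be recovered at analysis.

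**Working it through.** **Step 1: inputs from the protocol article (sample size section).** Two-sided Fisher's exact test, alpha 0.05; 25% infected; composite rate 1% in uninfected and 2% in infected women; 8,000 women for 90% power; 25% loss to follow-up; 10,000 enrolled.

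**Step 2: reproduce the plan's own figure.** For 2,000 infected at 2% against 6,000 uninfected at 1%, simulation with 10,000 repetitions gives 89.2% power, and the normal approximation gives 90.2%. The stated 90% is reproduced. The other rows of Tables 3 and 4 also reproduce within 2 points. All of these calculations assume equal detection in both groups.

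**Step 3: group sizes for the bias check.** Evaluable women: 10,000 × (1 − 0.25) = 7,500. Infected: 7,500 × 0.25 = 1,875. Uninfected: 7,500 − 1,875 = 5,625.

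**Step 4: no true effect, unequal detection.** Let d be the percentage points that extra detection adds in infected women. The observed rates are then 1% + d (infected) and 1% (uninfected). Rejection probability = the sum of the two binomial probabilities over all tables with a two-sided Fisher p-value of at most 0.05. Extra events = 1,875 × d.

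| d (points, assumed) | Expected extra events | Probability of a false significant result |
|---|---|---|
| 0 | 0 | 4.3% |
| 0.05 | 0.9 | 4.8% |
| 0.1 | 1.9 | 6.1% |
| 0.2 | 3.8 | 10.7% |
| 0.3 | 5.6 | 18.2% |
| 0.5 | 9.4 | 39.5% |

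**Step 5: what d would require.** Let q be the share of composite events that depend on imaging, and r the ratio of their detection in infected to uninfected women. The observed rate in infected women is 1% × [(1 − q) + q × r], so d = 1% × q × (r − 1). Simulated rejection with 7,500 women:

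- q = 25%, r = 1.25: d = 0.06 points, risk ratio 1.06, rejection 5%.
- q = 50%, r = 1.5: d = 0.25 points, risk ratio 1.25, rejection 14%.
- q = 50%, r = 2: d = 0.5 points, risk ratio 1.50, rejection 39.5%, which matches Step 4.
- q = 75%, r = 2: d = 0.75 points, risk ratio 1.75, rejection 68%.

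The document gives neither q nor r, so every row with d above zero is an assumption. The calculation uses the unadjusted test of the power section, not the adjusted model planned for the final analysis.

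**Step 6: which components are exposed to this.** CNS malformations and hydrops can be found by imaging. Fetal demise and neonatal death are events. Microcephaly rests on head circumference. Eye, hearing and neurological findings come from examinations scheduled for all infants. The last three groups are much less affected.

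**The case against.** **The text does not say that only exposed infants are recorded.** A reader might infer that radiology in unexposed infants is never captured. The sentence does not contain that word, the section refers the reader to Table 1 for more information, and Table 1 has no exposure condition. This stands: the documents support a conflict to be reconciled, not an established exclusion.

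**The added fetal imaging is modest.** The text schedules one scan, subject to country and local guidelines, soon after the positive test. All women already have a scan in each trimester. To change the composite, the added scan must show something that the routine scans, the delivery visit and four infant examinations all miss. This stands, and it is a reason to take the lower rows of the table seriously. It does not answer the infant imaging problem.

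**Bias is not demonstrated.** A reader might infer that the composite is biased as designed. The documents give no detection rates, and at 0.05 or 0.1 points the false-positive rate barely moves. An excess of 0.2 points is already a 20% relative inflation of the whole composite. This also stands: it is a risk of unknown size.

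**Analysis rules belong in the SAP.** This is fair as far as the missing ascertainment sensitivity analysis goes. It does not cover the recording rule, which the article states in two conflicting ways and which a SAP cannot repair afterwards.

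**Conclusion.** The point holds as a risk of detection bias toward an association, confined mainly to CNS malformations and hydrops, together with a definite inconsistency between Study procedures and Table 1 on infant imaging. Reconciling the two in favour of Table 1 removes the recording problem but not the fact that imaging done on clinical indication may follow known exposure.

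The size cannot be determined from the document. Over the assumed range of 0.05 to 0.5 extra points, the false-positive rate runs from 4.8% to 39.5%, against 4.3% with equal detection. This rests on a 1% true rate in both groups, 25% infected, 25% loss and an unadjusted Fisher test.

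The severity is should-fix. The documents do not support calling the primary comparison invalid, because most components are assessed on one schedule for everyone and no extra-detection rate is known.

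**What to change.** 1. Reword the radiology sentence in Study procedures so that imaging done for clinical care is recorded for all infants regardless of exposure, in line with Table 1. Settle this during data collection, because unrecorded imaging may not be recoverable later.
2. Keep the primary composite as defined. Pre-specify a sensitivity analysis that counts only events found by assessments scheduled identically for everyone: the per-trimester ultrasound, delivery, and the birth, 3-, 6- and 12-month examinations. Events seen only on the infection-triggered scan or on clinically ordered imaging are left out of that version. State which scan counts as the routine one in each trimester, and interpret the primary result alongside this analysis.

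A further option is to redefine the primary composite itself on uniform assessments. That would discard true malformations seen only on clinical imaging, in a study meant to describe the full range of outcomes, so the restriction fits better as a sensitivity analysis.

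The cost is some additional data entry for unexposed infants and one more analysis. No procedure is added or removed for any participant.
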